## Abstract

**Background:**

Pain is a negative factor in the recovery process of postoperative patients, causing pulmonary alterations and complications and affecting functional capacity. Thus, it is plausible to introduce transcutaneous electrical nerve stimulation (TENS) for pain relief to subsequently reduce complications caused by this pain in the postoperative period. The objective of this paper is to assess the effects of TENS on pain, walking function, respiratory muscle strength and vital capacity in kidney donors.

**Methods/design:**

Seventy-four patients will be randomly allocated into 2 groups: active TENS or placebo TENS. All patients will be assessed for pain intensity, walk function (Iowa Gait Test), respiratory muscle strength (maximal inspiratory pressure and maximal expiratory pressure) and vital capacity before and after the TENS application. The data will be collected by an assessor who is blinded to the group allocation.

**Discussion:**

This study is the first to examine the effects of TENS in this population. TENS during the postoperative period may result in pain relief and improvements in pulmonary tests and mobility, thus leading to an improved quality of life and further promoting organ donation.

**Trial registration:**

Registro Brasileiro de Ensaios Clinicos (ReBEC), number RBR-8xtkjp.

## Background

Organ donation has grown exponentially in Brazil, which is directly reflected by the significant increase in the number of transplants. A successful transplant affects both the lifespan and quality of life of patients. A renal graft from a living donor provides a 10 to 12% better chance of survival at one year [1]. There are several methods used to remove a kidney, and all are designed to minimize the harm to the donor. Methods that have been used since 1995 include lumbotomy, the subcostal access route and laparoscopic access routes [2-4].

The postoperative complications in patients who underwent nephrectomy can be divided into mechanical, pulmonary, vascular and operative wounds [5]. The major pulmonary complications during this period included the following: atelectasis, pneumothorax, pulmonary congestion, pneumonia and hypoxemia [6]. Pain is another factor that negatively influences the postoperative outcomes of patients, even with the administration of analgesics, including the most widely used opioids [7]. The major difficulty when using opioids is calculating the minimum concentration for effective analgesia, as overuse can lead to cough suppression, can limit effective sputum expulsion and can cause dizziness, nausea, vomiting, sedation, urinary retention and constipation, which are known side effects of opioids [8]. For these reasons, other non-pharmacological methods of pain control can help limit the use of opioids and reduce side effects [7].

Transcutaneous electrical nerve stimulation (TENS) is considered to be a non-pharmacological intervention strategy used for physical therapy pain relief with minimal side effects [9]. The use of TENS activates opioid receptors, which reduce the activation of the nociceptive sensory pathways and provide pain relief [10-12]. TENS has been used as a therapeutic option to control chronic and acute pain since the early 1970s. Its postoperative use following cardiac and thoracic surgery provides decreased analgesic consumption, lower incidence of pulmonary complications (such as atelectasis) and improved pulmonary function [13,14]. However, the positive effects of TENS have not been consistent. Some researchers found that TENS was not effective in all patients, especially those with more severe postoperative pain. Additionally, the declines in lung function and ventilation did not always responded positively after the use of TENS. Therefore, the actual role of TENS in controlling postoperative pain and its consequences remains controversial [6,13,15].

There has been a significant increase in the rate of kidney transplants performed using living donors in recent years, raising questions regarding the short- and long-term effects of this procedure, such as whether there would there be a difference in pain intensity or changes in pulmonary function and donor independence or functionality in the postoperative period after the use of TENS. Moreover, no previous studies were found in the literature that investigated the effects of TENS in this population. For these reasons, we decided to conduct a prospective randomized controlled study to follow kidney donors who underwent lumbotomy or subcostal nephrectomy to evaluate the effect of TENS on pain, walking function, respiratory muscle strength and vital capacity.

## Methods and design

### Study design

This study is a prospective randomized controlled and double-blind. Seventy-four patients will be randomly distributed into two groups: active TENS + analgesics (n = 37) and placebo TENS + analgesics (n = 37). Randomization will be performed by an investigator not involved in data collection using the sequentially numbered, opaque sealed envelopes (SNOSE) allocation concealment method [16,17]. Patients will be admitted one day before surgery and will undergo group randomization on the first day of the postoperative period. After randomization, the patients will be assessed for pain intensity, respiratory muscle strength, vital capacity and walking function before and after the use of TENS. The present study was approved by the Research Ethics Committees of University of the City of Sao Paulo and Federal University of Sao Paulo. All participants will receive written and verbal information on the aims and procedures of the study and will sign a consent form to agree to participate in the study.

All patients will be advised on the assessments that will be performed, including general information on the surgical procedure (type and size of the incision, sedation, intubation and need for admission to the Intensive Care Unit). The study flow diagram is presented in Figure 1.

**Figure 1 F1:**
[figure not shown]
Study flow diagram of the randomized controlled trial.

### Participants

This study will be conducted in the Kidney and Hypertension Hospital - Oswaldo Ramos Foundation, a supplementary service of the Federal University of Sao Paulo. The study will include 74 living kidney donors who underwent nephrectomy performed by two approaches: lumbotomy and the subcostal route. The route choice is dependent on the team performing the procedure, and these teams operate alternately on weekdays.

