### Inclusion criteria

• All living kidney donors undergoing nephrectomy by lumbotomy or the subcostal route;

• At least 18 years old and of either sex;

• Without acute or chronic pulmonary disease;

• Ability to perform the necessary physiotherapy maneuvers and measures;

• Pain intensity at rest greater than or equal to 2 and less than or equal to 7 on a numeric rating scale (0–10)

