#### Data analysis

The sample size was calculated considering a difference of two points in the verbal numeric pain scale between the TENS active and placebo groups and an estimated standard deviation of 3 based on data from a previous study [25]. For a significance level of 0.05 and 80% power, it was estimated that 37 participants would be required in each group (Minitab, v.15, State College, PA).

The statistical analysis will be performed on an intent-to-treat basis. The effects of the intervention on pain intensity, pulmonary function, and walking capacity, will be calculated using independent samples t tests for normally distributed data. Data not normally distributed will be compared using Mann–Whitney U tests. The level of significance will be set at *α* = .05. The data will be analysed using SPSS software (v.17; SPSS Inc; Chicago, IL) by an investigator who is blind to group allocation.

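### Surgical route is known before randomisation, but the tests named for the analysis cannot use it; the cost is modest precision, not bias

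*Protocol article*

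**What the plan says.** The Participants section describes the population as follows: "The study will include 74 living kidney donors who underwent nephrectomy performed by two approaches: lumbotomy and the subcostal route". It then says how route comes about: "The route choice is dependent on the team performing the procedure, and these teams operate alternately on weekdays". The Inclusion criteria admit both routes and set no quota for either.

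The Study design section sets equal groups of 37. It describes the allocation as done "using the sequentially numbered, opaque sealed envelopes (SNOSE) allocation concealment method", and says that patients "will undergo group randomization on the first day of the postoperative period". The incision appears once more in that section, in a sentence about what patients will be advised: "including general information on the surgical procedure (type and size of the incision".

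For pain, pulmonary function and walking, the Data analysis section says that effects "will be calculated using independent samples t tests for normally distributed data", with Mann–Whitney U tests where data are not normal. The sample size in the same section rests on a 2-point difference, a single SD of 3, a 0.05 significance level and 80% power.

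**The concern.** The outcomes are pain at rest, on coughing, during the breathing tests and while walking, together with respiratory pressures, vital capacity and gait. Incision site could plausibly affect all of them. Because route follows team and team follows weekday, the three form one known grouping of patients, and membership is settled before the envelope is opened.

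The tests named for the analysis compare two groups and accept no covariate. Two things follow if the routes differ in outcome. Where the arms happen to differ in their mix of routes, the estimated TENS effect moves with that mix and nothing in the analysis corrects it. And the between-route variance stays in the standard error although it could be removed. With 37 per group only just reaching 80% power, there is little precision to give away.

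**Working it through.** **Inputs from the Data analysis and Study design sections.** Difference 2 points, SD 3, alpha 0.05, power 80%, 37 per group, 74 in all. Sidedness is not stated; two-sided is taken because it is what reproduces the stated figure.

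**Inputs assumed, because the documents do not give them.** The share *p* of one route (0.5, with 0.3 as a check) and the mean pain difference *g* between routes (0 to 3 points).

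**1. The plan's own figure.** Normal approximation: n = 2 × (1.960 + 0.842)² × 3² / 2² = 35.3, so 36 per group. With the t distribution the answer is 36.3, so 37, as stated. Power at 37 per group is 80.8%. A one-sided calculation gives 28 and does not match.

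**2. Chance imbalance without stratification.** With 37 of 74 allocated to each arm, the number on a given route in one arm is hypergeometric. The between-arm difference in route share has these properties:

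| Route split | SD of difference | P(15 percentage points or more) | P(20 percentage points or more) |
|---|---|---|---|
| 50:50 | 11.7 points | 16% | 6% |
| 30:70 | 10.7 points | 20% | 7% |

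An imbalance *d* moves the unadjusted estimate by *d* × *g*. At *d* = 0.20 that is 0.2 pain points for *g* = 1 and 0.4 for *g* = 2. The planned standard error is 3 × √(2/37) = 0.70, so these shifts are 0.2/0.70 ≈ 0.29 and 0.4/0.70 ≈ 0.57 standard errors.

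**3. Power with route in the model, if the SD of 3 is the total SD.** Residual variance = 9 − p(1 − p)g². The t test then has 71 degrees of freedom instead of 72. The small loss from imbalance between arms is ignored here; step 5 includes it.

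| Route difference *g* | Residual variance at 50:50 | Residual SD | Power adjusted, 50:50 | Power adjusted, 30:70 |
|---|---|---|---|---|
| 0 | 9 − 0 = 9.00 | 3.00 | 80.7% | 80.7% |
| 1 | 9 − 0.25 = 8.75 | 2.96 | 81.8% | 81.6% |
| 2 | 9 − 1.00 = 8.00 | 2.83 | 85.1% | 84.4% |
| 3 | 9 − 2.25 = 6.75 | 2.60 | 90.4% | 88.9% |

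The unadjusted comparison has 80.8% power throughout.

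**4. If the SD of 3 is instead a within-route SD.** The total variance becomes 9 + p(1 − p)g². At 50:50, unadjusted power is 79.7%, 76.5% and 71.6% for *g* = 1, 2 and 3. Adjusting removes the added variance and returns power to 80.7%. The document does not say which kind of SD the 3 is.

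**5. Simulated error rates** (8,000 runs each, about 50:50 split, total SD 3):

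| Allocation and analysis | Type I error, *g* = 1 | Type I error, *g* = 2 | Power, *g* = 1 | Power, *g* = 2 |
|---|---|---|---|---|
| Unstratified, unadjusted | 5.3% | 4.8% | 80.8% | 80.4% |
| Unstratified, adjusted | 5.3% | 5.1% | 81.7% | 84.6% |
| Stratified, unadjusted | 4.8% | 3.9% | 81.1% | 81.3% |
| Stratified, adjusted | 5.0% | 5.2% | 81.9% | 85.0% |

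Most of the gain comes from the model. Stratifying the envelopes while keeping the unadjusted test recovers little power and makes the test conservative at *g* = 2.

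**The case against.** The strongest reply is that an unadjusted two-group test is valid in a randomised trial. Route is fixed before randomisation, so it cannot differ systematically between arms, and chance imbalance is already covered by the test's error rate. That stands, and the simulated type I errors bear it out. A reader might infer from the link between route, team and weekday that the TENS effect is confounded with the surgical team. It is not: that link prevents separating route from team, which the TENS comparison does not need.

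A reader might also infer that the allocation is unstratified. The article names a concealment method and is silent on how the sequence is generated. A condensed article may leave that to the full protocol, and sealed envelopes are compatible with one stack per route. The point therefore rests on the analysis section, which does name its tests.

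Nor does the article show that route is entered as data. The sentence that mentions incision type concerns what patients are told. Equally, it does not show that route goes unrecorded.

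Finally, no passage says that the two routes differ in pain. The Discussion reports that TENS results vary after different chest operations, but that is not evidence about lumbotomy against subcostal nephrectomy. The entry range of 2 to 7 for resting pain also limits how far routes can differ at rest before treatment. It does not limit pain on coughing, breathing tests or walking. So the size of the gain is uncertain and may be close to nil.

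**Conclusion.** The point holds as a matter of efficiency. The analysis section commits to tests that cannot use a grouping which the protocol itself describes and which is known for every patient at randomisation. There is no systematic bias, and type I error is nominal.

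At a 50:50 split and a total SD of 3, the power forgone is about 1 percentage point if routes differ by 1 point, about 4 if by 2 and about 10 if by 3; it is nil if they do not differ. A 30:70 split gives slightly smaller gains. All of this depends on an assumed split and an assumed route difference.

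A reader might conclude that the sample size is wrong. The documents do not support that: 37 per group reproduces, and with route in the model it keeps about 80% power or more under either reading of the SD. The change is worth making because it is nearly free, not because the planned result would be invalid.

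**What to change.** In the Data analysis section, replace the unadjusted tests for the continuous outcomes with one prespecified linear model (ANCOVA): post-TENS value on treatment, surgical route and pre-TENS value. The pre-TENS value is already collected for each outcome. The gain from including it is not quantified here, because the documents give no correlation between the two measurements. The level of assistance in the gait test is an ordered category and falls outside this model.

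State that route is captured for every patient as an analysis variable.

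If the full protocol does not already stratify the envelopes by route, and they are not yet prepared, stratifying is an optional addition. It should accompany the adjusted model rather than stand in for it.

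Cost: one degree of freedom for route and one for baseline, one data field, and a second stack of envelopes if stratification is taken up. The sample size and the clinical procedures do not change.

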### Inclusion criteria

• All living kidney donors undergoing nephrectomy by lumbotomy or the subcostal route;

• At least 18 years old and of either sex;

• Without acute or chronic pulmonary disease;

• Ability to perform the necessary physiotherapy maneuvers and measures;

• Pain intensity at rest greater than or equal to 2 and less than or equal to 7 on a numeric rating scale (0–10)

### Exclusion criteria

• All living kidney donors who have previous experience with TENS;

• Need for surgical intervention on another organ in addition to the kidney;

• Surgical reintervention during the data collection period;

• Required mechanical ventilation for more than 12 hours;

• Died within 6 hours of the operation

### Intervention

#### Application of active TENS

The use of active TENS will be conducted with a Neurodyn Portable TENS unit (IBRAMED) with two channels. The generator emits asymmetric, balanced, biphasic pulses. Two self-adhesive electrodes (VALUTRODE - 9 × 5 cm) will be placed in parallel on both sides of the incision with a 3-cm distance between them. The duration of the TENS application will be 1 hour at a frequency of 100 Hz and a pulse duration of 100 microseconds [18]. The intensity (amplitude) will be increased until the patient is able to feel a strong but comfortable tingling sensation. Patients will be asked about the intensity of the TENS every 10 minutes. In the case of sensory habituation, the amplitude will be increased until the individual again feels a strong but comfortable tingling sensation. The application will be performed on the first day of the postoperative period.

#### Application of placebo TENS

The use of the placebo TENS will be performed with an apparatus identical in appearance to the active TENS (Neurodyn Portable TENS, IBRAMED) that is specially designed for this study. The device remains active only during the first 30 seconds of application. After the initial 30 seconds, the current amplitude will gradually decrease over 15 seconds until it reaches the zero value, thereby interrupting the emission of electric current. The unit will remain inactive for the rest of the application [19]. The placebo TENS device displays a light during the entire application, indicating to the patient that the device is active. Patients will be informed that TENS may cause a slight tingling sensation or no sensation during the procedure.

They will be asked every 10 minutes about the intensity of TENS, reinforcing the idea that lack of sensation occurs in most cases due to habituation to the electric current. Patients will be observed throughout the administration of TENS [20]. The mode of application of the electrodes and the duration of the placebo TENS will be the same as described in the active TENS.

#### Outcome measures

***Primary outcome: *****pain intensity**

To evaluate pain intensity, an 11-point numeric rating scale (NRS) will be used, where 0 represents no pain and 10 represents the most intense pain imaginable. The assessment will be conducted at rest, during coughing and during respiratory tests (maximal inspiratory and expiratory pressures and vital capacity) and walking function (Iowa Gait Test) before and after administration of TENS [21].

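### The primary outcome is pain under four to six conditions with no lead score, while the sample size covers one comparison of an unidentified pain score

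*Protocol article*

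**What the plan says.** Under the primary outcome heading, the protocol article chooses the scale: "To evaluate pain intensity, an 11-point numeric rating scale (NRS) will be used". It then lists when the scale is applied: "The assessment will be conducted at rest, during coughing and during respiratory tests (maximal inspiratory and expiratory pressures and vital capacity) and walking function", each "before and after administration of TENS". No situation is given priority over another.

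The Data analysis section bases the sample size on one contrast, "considering a difference of two points in the verbal numeric pain scale between the TENS active and placebo groups". For the spread of the scores it relies on "an estimated standard deviation of 3 based on data from a previous study". From these inputs it concludes: "For a significance level of 0.05 and 80% power, it was estimated that 37 participants would be required in each group". It does not say whether the difference and the standard deviation (SD) refer to pain at rest, on coughing or during a test.

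The same section says that effects on pain intensity, pulmonary function and walking "will be calculated using independent samples t tests for normally distributed data", with Mann–Whitney tests otherwise. One level serves all analyses: "The level of significance will be set at" 0.05. No way of combining the pain scores, ranking them or adjusting for their number is described.

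Pain at rest is singled out only in the inclusion criteria, which require a score from 2 to 7.

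**The concern.** The primary outcome is defined as a set of scores, but the trial is sized as if there were one. The two sections cannot both describe the same primary test.

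Two things are at stake. First, the error rate and the power of the primary claim depend on a success rule that is not written down. Second, the scores may disagree: TENS might help at rest and not on coughing or walking. The Background itself says that earlier results with TENS have been inconsistent. In that case nothing settles what the trial concluded, and the lead score could be chosen after the data are seen.

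**Working it through.** **Inputs from the protocol article.** Difference 2, SD 3, significance level 0.05, power 80%, 37 per arm (Data analysis and Study design). The number of primary pain scores, k, comes from the primary outcome paragraph:
- k = 4: rest, cough, respiratory tests as one rating, walking.
- k = 6: rest, cough, PImax, PEmax, vital capacity, walking.

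**Assumptions.** Tests are two-sided. The scores share one common correlation r; the article gives none, so a range is shown.

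**1. The plan's own figure.** The standardised difference is 2/3.
- Normal approximation: n = 2 × (1.960 + 0.842)² × (3/2)² = 35.3, so 36 per arm.
- Two-sample t test (noncentral t): 36.3, so 37 per arm, with power 80.8% at 37.
- A one-sided t test would need 28.5, so 29, which does not match.

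The stated 37 is therefore correct for one two-sided comparison at the full 0.05.

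**2. If any one significant score counts as success.** With no true effect and independent scores, the chance of at least one false positive is 1 − 0.95^k:
- k = 4: 1 − 0.8145 = 18.5%
- k = 6: 1 − 0.7351 = 26.5%

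For k equally correlated two-sided tests at 0.05:

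| r | k = 4 | k = 6 |
|---|---|---|
| 0 | 18.5% | 26.5% |
| 0.5 | 15.6% | about 21% |
| 0.7 | about 13% | 16.4% |
| 0.9 | 9.4% | 10.8% |

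**3. If every score must be significant.** The chance of a false positive stays at or below 5%. Suppose the 2-point difference and SD of 3 hold for every score. Each test then has 80.8% power, and the chance that all succeed cannot exceed that. With independent scores it is 0.808⁴ = 43% or 0.808⁶ = 28%. Simulation of 40,000 trials with 37 per arm at r = 0.9 gives about 71% (k = 4) and 68% (k = 6). Both are below the stated 80%.

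**4. If all scores stay primary with a Bonferroni split.** Power for each single score at 37 per arm is 62.1% for k = 4 (level 0.05/4 = 0.0125) and 56.4% for k = 6 (level 0.05/6 = 0.0083). Restoring 80% per score by t test needs 52 or 57 per arm.

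**5. Whether the sizing figures suit rest pain.** Scores confined to 2–7 have an SD of at most (7 − 2)/2 = 2.5, which is below 3. A patient who enters at 2 can improve by 2 points at most. The limit applies to rest pain at entry; scores after treatment can fall outside 2–7. It does not rule the figures out for rest pain, but it means they should not be carried over without a reason.

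**The case against.** Several stronger readings are tempting and go beyond the text.

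- *Six scores, each tested at 0.05, any one of which makes the trial positive.* A reader might infer this, but the article does not say it. The three respiratory measures sit together in a parenthesis and may share one rating. Separate tests per condition are an inference from a single significance level and two-group tests with no method of combination. No success rule is written at all, so the inflated error rate is conditional on an any-one rule.
- *The error is several times 0.05.* The scores come from the same patient on the same scale, so independence is implausible. At r = 0.9 the rate is about twice 0.05. The 26.5% figure is an outer limit.
- *Bonferroni would leave the trial with 56% power.* That is power for one score. If a 2-point effect held on all six, the chance of winning at least one adjusted test would be about 89%, 83% and 72% at r = 0.5, 0.7 and 0.9.
- *Pain during the tests is a poor endpoint because patients choose their effort.* The article says that patients are urged to maximal effort in the pressure tests and told to walk as fast as is safe, although it also mentions their own pace. Coughing depends on effort too. The point does not need this argument.
- *Eligibility makes rest pain the primary score.* An entry criterion does not name an endpoint.

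It is also fair to say that order of testing and adjustment are often left to an analysis plan, which is not shown here. What remains is narrower. Which measurement is primary, and which one the sample size refers to, are matters for the protocol. The article defines the first as a whole set and the second as one unnamed score.

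**Conclusion.** The point stands in this limited form: there are four to six primary pain scores and no lead, and the sample size is arithmetically correct for a single comparison that is not tied to any of them. The consequence depends on the unstated success rule. Under an any-one rule the false positive rate is about 9–16% (four scores) or 11–21% (six), for r from 0.9 down to 0.5. Under an all-must-succeed rule the error rate is controlled and the design is underpowered against its stated 80%. Both results rest on an assumed common correlation. The documents do not support saying that the trial will be declared positive on any one score, only that nothing rules it out.

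**What to change.** Before unblinding, name one pain condition as the single primary endpoint, and say whether the score after treatment or the change is compared. The best choice is the condition from which the 2-point difference and SD of 3 were taken. Post-treatment pain at rest is one candidate. If a different condition is chosen from the one behind those figures, justify carrying them over; for rest pain, address the 2–7 entry range.

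Make the remaining pain conditions secondary, or test them in a fixed order after the primary, each only if the one before is significant.

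The cost is about one paragraph, with no added patients or visits as long as the difference and SD apply to the named score. If they do not, the 37 per arm needs recalculating. The price is that the other pain scores can no longer carry the primary claim on their own.
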